### Procedure

After screening, eligible participants will be contacted by a study researcher who will arrange a one-on-one meeting (Figure 1, CONSORT flow diagram). During the meeting, the participant will receive a detailed explanation of the study, and its requirements and expectations from the researcher. They will also be provided with an information sheet providing the same information and outlining their rights to confidentiality and to withdraw from the study at any stage without consequence. Once the participant has had the opportunity to confirm their understanding of the project and have any questions answered, they will be asked to sign an informed consent form.

A study researcher will set up and initiate a GENEActiv activity monitor [47] for each participant, including programming the participant’s code number, date of birth, height, and handedness. Each monitor will be programmed to start collecting data from set up. Study participants will be required to wear the monitor on their non-dominant upper arm and will be provided with detailed instructions on how to wear the device. Participants will be instructed to wear it continuously throughout day and night for one week after the first meeting.

Eight days later, participants will meet with the researcher again to return the activity monitor. The study facilitator will check if sufficient data have been collected by the device (i.e., at least five days of wear with a minimum 16 h wear per day) [48]. If the participant fails to wear the activity monitor for the minimum time specified, they will be asked to wear it again for another seven days. At this second meeting, participants will also be asked to complete web-based baseline questionnaires using a provided tablet (Time 1).

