After the second meeting, participants will be emailed a personalised login/password, and link to the website so they are able to login to the web-based *PATHS* study platform used to deliver the tailored intervention messages. Participants will be automatically randomly allocated online in an equal ratio to one of the four possible study conditions; a block randomisation will be used with block size of 16. If allocated to one of the three intervention conditions, they will be able to complete the first intervention session on the website immediately after completing the baseline assessments. If allocated to the control condition, they will receive an email directing them to the *Library* site for physical activity relevant information. The *Library* is a sub-section of the website with non-tailored evidence-based information about physical activity,

Across all conditions, participants will be encouraged to use and interact with the web-based *PATHS* platform for three consecutive months, completing sessions every fortnight. At the end of month three, participants will meet with the researcher and will be provided with a GENEActiv activity monitor to be worn for one week immediately post-intervention to assess physical activity. Participants will meet with the researcher again one week after they received the activity monitor to complete the post-intervention questionnaires and return the activity monitor (Time 2). All researchers collecting the data will be blinded to the allocation of participants’ study condition.

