5	Experiencing barriers to being active and staying motivated; reasons for falling back into bad habits; relapse prevention	- Physical activity (10) - Weight (1) - Behavioural barriers (2) - Open question re-evaluating short term goal for PATHS (1) - Habit development (2) - Feedback on the session after tailored advice (1)	- Welcome based on the condition (3) - Self-regulation: Physical activity progress feedback (52) - Habit: Maintaining positive habits – coping planning (4) - Motivation: Relapse prevention based on the main barrier selected with an emphasis on staying motivated (10) - Self-regulation: Relapse prevention based on the main barrier selected with an emphasis on staying motivated and self-regulating (10) - Habit: Relapse prevention based on the main barrier selected with an emphasis on staying motivated/self-regulating and maintaining positive habits (10) - Conclusion based on the condition (3)	1.2. Problem solving 1.7. Review outcome goal(s) 7.3. Reduce prompts/cues 8.2. Behaviour substitution 8.4. Habit reversal 11.2. Reducing negative emotions 12.3. Avoidance/ reducing exposure to cues for the behaviour	Self-efficacy, intrinsic motivation, goals, intentions, knowledge, attitudes, perceived behavioural control, emotions, self-regulation, habits, cues-to-action, behavioural barriers
6	Summary: staying motivated, self-regulating and maintaining habits	- Physical activity (10) - Weight (1) - Habit Automaticity Index (4 questions) - Feedback on the session after tailored advice (1)	- Welcome based on the condition (3) - Self-regulation: Physical activity progress feedback with graph (52) - Self-regulation: Weight changes throughout the program with graph (16) - Motivation: Tips to stay motivated (1) - Self-regulation: Tips to stay motivated and to self-regulate PA (1) - Habit: Tips to stay motivated and to self-regulate PA and to follow newly developed routines (1) - Motivation: Success stories from other hospital employees who increased their PA (1) - Conclusion based on the condition (3)	2.2. Feedback on behaviour 2.7. Feedback on outcome (s) of behaviour 5.1. Information about health consequences 5.6. Information about emotional consequences 6.3. Information about others’ approval 8.1. Behavioural practice/rehearsal 9.2. Pros and cons	Self-efficacy, Intrinsic motivation, Autonomous Motivation, Intention to maintain the behaviour, Habit

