### Measures

Table 3 describes measures that will be taken during the study, specifying the type of outcome assessed, the measurement tool used, the number of questions included, and the time points when the measures will be administered.

**Table 3 Tab3:** Measures taken at Time 1 and Time 2 and outcomes assessed

Measurement tool	Reference	Number of items		Outcome
		Time 1	Time 2	
		(baseline)	(3 months)	
Survey measures				
Confirmation of eligibility to participate in the study	N/A	8	-	Eligibility
Physical Activity Readiness Questionnaire (PAR-Q)	[45]	8	-	Readiness to undertake PA
Demographics	Commonly used items	14	6	Age, sex, marital status, ethnicity, education, weight, height, house income, postcode
International Physical Activity Questionnaire (short version)	[68, 69]	7	7	Physical Activity
Job-related physical activity	From: International Physical Activity Questionnaire (long version) [68]	8	8	Job-related physical activity
The Pittsburgh Sleep Quality Index (PSQI)	[70]	9	9	Sleep
Theory-relevant determinants of physical activity	Individual items taken from different questionnaires	30	30	Motivation, attitudes towards regular physical activity, outcome expectations, perceived behavioural control, subjective norms, intentions, barriers self-efficacy, action planning and coping planning, self-efficacy, goal facilitation and goal conflict
Self-report behavioural automaticity index	[77]	8	8	Behaviour automaticity
Personal Need for Structure Scale	[78]	12	-	Personal Need for Structure
Physical activity intentions	[72]	3	3	Physical Activity Intentions
Depression Anxiety Stress Scale 21 (DASS 21)	[79]	21	21	Depression, Anxiety, Stress
SF 12	[80]	12	12	Quality of life
Physical Activity Neighbourhood Environment Survey (PANES)	[81]	17	-	Perceptions of the environment in relation to PA
Internet use and access to the intervention	Items developed for this study	-	4	Internet use and access to the intervention
Internet self-efficacy scale	[83]	9	-	Internet self-efficacy
SUS and satisfaction	[82]	-	16	SUS and satisfaction
Physical advice acceptability	[66]	-	15	Physical advice acceptability
Delivery mode usability	[66]	-	5	Delivery mode usability
Usefulness questions	[66]	-	5	Intervention usefulness
Format-related questions	[66]	-	9	Format
Total items		158	158	
Outcome measures and moderators				
Physical activity objectively measured with GENEActiv	[47, 67]	✓	✓	Objectively measured physical activity

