### Study hypotheses

We hypothesise significant increases in physical activity between baseline and 3-month follow-up in the three intervention conditions but no change in physical activity levels in the control groupWe hypothesise that increases in physical activity at 3-month follow-up will be greatest in the habit intervention condition with smaller changes for the self-regulation and motivation conditions.We hypothesise that participants allocated to the habit condition will have maintained the physical activity changes over time relative to the self-regulation, motivation, and control conditions at 3-month follow-upWe hypothesise that higher engagement in the program (e.g., frequency of logins, number of sessions completed, reported relevance and usefulness of the sessions content) will lead to greater change in physical activity at 3-month follow-up in all intervention groups.We hypothesise that the effects of the habit condition on physical activity behaviour will be mediated by the self-reported habit development, effects of the self-regulation condition will be mediated by self-efficacy and planning, and the motivation condition will be mediated by the social cognitive variables of attitudes, motivation, and intention.

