### Study analysis

The intervention will be evaluated following the recent guidance on process evaluation for complex interventions [86]. Data will be analysed using generalized linear mixed modelling (GLMM) [87] with a 4 (condition: control, motivation, self-regulation, habit) × 2 (time: baseline, 3-month follow-up) mixed-model design, accounting for nesting within hospital. Models will be conducting to compare change between conditions of the primary outcome (physical activity) and secondary outcomes (e.g., theory-derived psychological constructs, DASS21, MOS-SF12, and absenteeism). Mediation analyses will be conducted using path analytic models using Preacher and Hayes’ bootstrapped approach for multiple mediation [88]. Separate path models will be conducted for each condition. Each condition will be represented by a dichotomous dummy-coded variable (0 = did not receive intervention component, 1 = received intervention component). Each condition variable will be set as a predictor of physical activity at follow up with motivation and intention (motivation condition), perceived behavioural control and planning (self-regulation condition), and self-reported habit (habit condition) as multiple mediators in each analysis, respectively. Baseline physical activity will be included as a control variable. Intention-to-treat (baseline carried forward) will be utilised for missing data from drop-out. Other missing data will be imputed using multiple imputation with chained equations [89]. Both intention-to-treat and completers analyses will be reported.

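### The mediation models test hypothesis 5 only in part, and the follow-up mediators are recorded after the activity week they are meant to explain

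*Protocol article*

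**What the plan says.** Study hypotheses, hypothesis 5, assigns mediators to each condition. Habit is to work through self-reported habit development. For self-regulation, "effects of the self-regulation condition will be mediated by self-efficacy and planning". The motivation condition is to work through attitudes, motivation and intention.

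Study analysis then lists the mediators of the path models as "motivation and intention (motivation condition), perceived behavioural control and planning (self-regulation condition), and self-reported habit (habit condition"). The outcome is physical activity at follow-up. On covariates it says: "Baseline physical activity will be included as a control variable".

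Procedure fixes the order at follow-up. At the end of month three participants "will be provided with a GENEActiv activity monitor to be worn for one week immediately post-intervention to assess physical activity". Then: "Participants will meet with the researcher again one week after they received the activity monitor to complete the post-intervention questionnaires". Baseline follows the same order, with the monitor week first: "At this second meeting, participants will also be asked to complete web-based baseline questionnaires using a provided tablet (Time 1").

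Table 3 schedules the block "Theory-relevant determinants of physical activity" (30 items), the intention items (3) and the automaticity index (8) at Time 1 and Time 2 only.

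**The concern.** Two things do not fit together.

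First, the stated hypothesis and the model meant to test it use different mediator sets in two of the three conditions. If the plan is followed as written, two hypothesised mechanisms get no mediation test, and one construct that was not hypothesised gets one. If the discrepancy is left open, the choice between the two sets could be made once results are known.

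Second, a mediation model reads the mediator as lying between treatment and outcome. Here the follow-up mediator is recorded after the outcome week has ended. A participant who has just had an active week may report stronger intention, planning or habit because of it. The article's own theory section describes habit as growing out of repeated behaviour, so this reverse path is plausible.

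What is at stake is the mechanism claim. The Discussion and Implications sections present identification of mediators and active ingredients as a main contribution of the trial.

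**Working it through.** **Mediator sets side by side** (Study hypotheses against Study analysis):

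| Condition | Hypothesised | In the path model | Match |
|---|---|---|---|
| Habit | self-reported habit | self-reported habit | 1 of 1 |
| Self-regulation | self-efficacy, planning | perceived behavioural control, planning | 1 of 2 |
| Motivation | attitudes, motivation, intention | motivation, intention | 2 of 3 |

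Total: 1 + 1 + 2 = 4 of 6 hypothesised mediators are in a path model. Two are missing (self-efficacy, attitudes) and one is added (perceived behavioural control).

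The replacement is not a synonym. The section on theory-derived psychological constructs lists perceived behavioural control and self-efficacy as separate measures with separate sources. Nor is it forced by missing data: Table 3 lists attitudes, self-efficacy and perceived behavioural control at both time points.

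**Time order at follow-up** (Procedure, Table 3):

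1. End of month three: monitor handed out.
2. The following week: activity recorded. This is the outcome of the path model.
3. Return meeting: questionnaires completed. These supply the mediators.

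The one mediator measure repeated inside the programme is "Habit Automaticity Index (4 questions"), in sessions 1 and 6 of Table 2. Session 6 would normally precede the outcome week. However, Intervention delivery gives the fortnightly surveys to the three intervention groups, and Table 1 has no control column, so there is no comparable control value. Session 6 lists no intention, planning or self-efficacy items.

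**What the order can do to the estimate.** The article gives no figure for the mediation analysis, so there is nothing to reproduce. The following is an illustration under assumed values.

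- Condition X raises follow-up activity Y by t = 0.28 SD. This value is borrowed from the Sample size section.
- The mediator M is caused only by Y: M = λY + e, with Var(Y given X) = 1 and Var(e) = 1 − λ². M has no effect on Y, so true mediation is zero.
- Fitting M on X gives a = λt.
- Fitting Y on X and M gives b = Cov(Y, M given X) / Var(M given X) = λ / (λ² + 1 − λ²) = λ.
- Fitted indirect effect: ab = tλ². Share of the total effect: ab/t = λ².

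| λ | ab (SD) | Share of total |
|---|---|---|
| 0.2 | 0.28 × 0.04 = 0.011 | 4% |
| 0.3 | 0.28 × 0.09 = 0.025 | 9% |
| 0.5 | 0.28 × 0.25 = 0.070 | 25% |

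A large-sample simulation of the same set-up gave 0.0113, 0.0249 and 0.0689. Bootstrapping describes the sampling error of ab; it cannot tell which direction produced it. Adjusting for baseline activity does not close a path from follow-up activity to the follow-up mediator.

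**The case against.** Several stronger readings are tempting, and the document does not support them.

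- *A reader might infer that hypothesis 5 is not tested at all.* Four of six mediators match, and the habit condition matches completely. The hypothesis is tested incompletely, not left untested.
- *A reader might infer that self-efficacy and attitudes are never analysed.* Study analysis also compares change between conditions in the theory-derived constructs as secondary outcomes. The effect of condition on both can be estimated there. They are absent only from the mediation models.
- *A reader might infer that baseline mediator scores are ruled out as covariates.* The article says that baseline activity is included; it does not say that nothing else is. A fuller covariate list may sit in an analysis plan that is not shown. Adding the scores is therefore a recommended improvement, not a fault in the text.
- *A reader might infer that moving the questionnaire is a free remedy.* Baseline and follow-up now share the same order. Asking about plans and cues before the follow-up wear week, but not before the baseline one, would break that symmetry and could prime the primary outcome, perhaps differently in arms trained in planning and cue recognition.

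It is also fair to say that the gap is only one week after a three-month programme, that some constructs may barely move in that time, and that activity during the programme could shape answers given at hand-out too. The mismatch could in principle be settled by amending the hypothesis instead. The Discussion, however, again gives planning and self-efficacy as its example for self-regulation, though only as an example.

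What remains is the mismatch in two conditions, and a time order that does not support a directional reading.

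**Conclusion.** The point holds in limited form. Two of six hypothesised mediators enter no mediation model although both are collected at both time points, and one construct outside the hypothesis takes a place in the self-regulation model. This follows directly from the text and needs no assumption.

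Separately, the follow-up mediators are recorded after the outcome week, so the path models cannot distinguish mediation from activity influencing the answers. The size of any resulting bias is unknown. The 4% to 25% range rests on assumed coefficients of 0.2 to 0.5, on no true mediation and on a 0.28 SD effect; it shows what is possible, not what is expected.

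The primary comparison of physical activity between conditions does not depend on any of this. The matter should be corrected because mechanism is one of the trial's advertised findings.

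**What to change.** 1. In Study analysis, use the hypothesised mediators: self-efficacy and planning for self-regulation; attitudes, motivation and intention for motivation; self-reported habit for habit. Since barriers self-efficacy and self-efficacy are listed separately, state which one is meant. If perceived behavioural control is kept, label it exploratory. Cost: wording only, as all constructs are already measured.
2. Add each mediator's baseline score as a covariate beside baseline physical activity. Randomisation protects the path from condition to mediator but not the path from mediator to outcome. Cost: a few degrees of freedom; the scores are already collected.
3. Report the mediation results as associations at follow-up without an established time order, and limit the mechanism statements in the Discussion and Implications accordingly. Cost: a weaker claim.
4. As an alternative to item 3, the sponsor may collect the mediator items in all four arms at the existing monitor hand-out meeting. Cost: a split Time 2 survey, possible priming of the primary-outcome week, and loss of the matching baseline order. This would put the mediators before the outcome week but would not remove the influence of activity during the preceding three months. The choice should be made and recorded before follow-up data are seen.

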### Intervention content

#### Control condition

Participants assigned to the control condition will be provided with information about physical activity recommendations compiled in the *Library* and will have the opportunity to rate the content (ranging from 0 stars [*not interesting and not useful*] to 5 stars [*very interesting and very useful*]). The presentation order of the articles will move up or down on the list based on the ratings given by the platform users, with the ones rated the highest displayed at the top of the page. The information will be factual and non-personalised. BCTs used in the control group are: providing information about health consequences [49], providing information about social [50], environmental [51] and emotional consequences [52]. Websites that provide information only have not been shown to have strong effects on health behaviour change [27] and is effective as a control group in the current study as it provides a control for information load and contact with the study team.

#### Motivation condition

Participants assigned to the motivation condition will receive personalised messages based on BCTs to promote intention and self-efficacy to engage in physical activity [53]. Specifically, participants will be provided with advice on how to work towards their goals and to maintain motivation in the face of barriers [54, 55].

#### Self-regulation condition

Participants assigned to the self-regulation condition will receive the content from the motivation condition along with content promoting self-regulation. Specifically, participants will be encouraged to set outcome-specific goals [56] and to self-monitor their progress towards these goals by monitoring how much time they spent doing physical activity. They will also be prompted to form action and coping plans [57], specifying when, where and how they will perform their physical activities, and identifying barriers to their physical activity participation and how they might overcome them. Participants will be encouraged to specifically focus on self-monitoring in high risk situations [58], such as when they are tired or stressed and their capacity for self-regulation is most likely to be compromised [59, 60]. Participants will also receive information on managing multiple goals [61] and self-regulating the situation when competing activities arise (e.g., the desire to be active and healthy conflicts with other situational options such as watching TV and resting).

#### Habit condition

Participants assigned to the habit condition will receive the content from the motivation and self-regulation conditions along with content promoting habit development (e.g., recognising prompts to action and learning to act upon these prompts). Participants will receive information relevant to implementation intentions with context-specific prompts [62] (e.g., forming simple prompt-dependent plans to engage in physical activity when the prompt occurs). They will be asked to recognise and identify situational, contextual and time-based cues that can prompt them to be more active. Participants will be encouraged to develop a habit of instigating physical activity without having to consciously remember [63]. In order to do things automatically behavioural repetition of the same activity in the same contexts will be encouraged; participants will have the choice of which context they wish to do the activity.

